### Sample size considerations

The sample size is determined by the estimated risk in the group of patients randomized to usual care (control group, A, figure 1) and the risk observed in the groups that undergo cardiac imaging followed by subsequent treatment by a cardiologist as outlined in the protocol (groups B to D). Based on earlier studies in the Netherlands the 5-year-risk in the control group is assumed 24%[42]. The 5 year risk of cardiovascular morbidity and mortality among the IC patients that undergo cardiac imaging and subsequent treatment is based on the sum of **I) **the risk observed in those with stenosis in the main left coronary artery (group B, figure 1) plus **II) **the risk observed in those with limited vessel disease but no ischemia during the dobutamine stress test (group D) plus **III) **the risk observed in those with limited coronary vessel disease but with ischemia during the dobutamine stress test (group C).

The prevalence of these subgroups B to D in the arm of cardiac imaging and subsequent treatment is estimated to be 8% for B; 70% for D and 22% for C. Using the literature we have estimated the risk of cardiovascular morbidity and mortality for these groups of patients belonging to category B to D.

The 5-year risk of cardiovascular morbidity and mortality in these subgroups is 66% for those with stenosis of the left main coronary artery[41] (group B), 32.8% for those with cardiac ischemia during the stress test (group C) and 16.4% for those without cardiac ischemia (group D).

The estimates for patients in categories C and D are based on the assumption that those with cardiac ischemia have a doubling of risk compared with those without cardiac ischemia and that the risk of all groups combined should add up to 24%.

The effects of interventions performed by the cardiologist on the risk observed in PAD patients who undergo cardiac imaging are based on published international data from the ACC and AHA guidelines. These effects are for the two appropriate subgroups: 70% reduction in 5-year event rate using reperfusion therapy (PCI/CABG) for group B and 40% reduction in 5-year event rate using reperfusion therapy (PCI/CABG) for group C. Patients without cardiac ischemia (group D) will receive no treatment.

Based on these estimates, the 5-year risk of cardiovascular morbidity and mortality will be 17.4 % in the intervention group (the combined risk for groups B and C; 70% event reduction in the group with a risk of 66% applying to 8% of the population; 40% event reduction in the group of patients with a risk of 32.8% applying to 22% of patients), reflecting an estimated relative reduction in cardiovascular morbidity and mortality of 24%.

The total number of patients randomized to achieve this goal, with a two-sided alpha of 0.05 and 80% power will be 1222. For this calculation we used dedicated software ('Power', dr. [name], Erasmus Medical Center, Rotterdam, the Netherlands). A study of this size has a statistical power of 80% at a two-sided alpha level of 0.05. The reason for using interim analysis [43] is that on average fewer patients are needed in the study when the expected difference in the primary outcome variable is real or when no difference can be expected anymore, therefore increasing efficiency. Sequential analyses are performed on survival outcome variables according to the double triangular test as described by Whitehead [44] and implemented in the computer program PEST version 4 [45]. The sequential (interim) analyses will be performed every three months by an independent data safety monitoring board (DSMB).

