**Design:**

The GROUND study is designed as a prospective, multi-center, randomized clinical trial. Patients with peripheral arterial disease, but without symptomatic cardiac disease will be asked to participate. All patients receive a proper risk factor management before randomization. Half of the recruited patients will enter the 'control group' and only undergo CT calcium scoring. The other half of the recruited patients (index group) will undergo the non invasive cardiac imaging algorithm followed by evidence-based treatment. First, patients are submitted to CT calcium scoring and CT angiography. Patients with a left main (or equivalent) coronary artery stenosis of > 50% on CT will be referred to a cardiologist without further imaging. All other patients in this group will undergo dobutamine stress magnetic resonance (DSMR) testing. Patients with a DSMR positive for ischemia will also be referred to a cardiologist. These patients are candidates for conventional coronary angiography and cardiac interventions (coronary artery bypass grafting (CABG) or percutaneous cardiac interventions (PCI)), if indicated. All participants of the trial will enter a 5 year follow up period for the occurrence of cardiovascular events. Sequential interim analysis will take place. Based on sample size calculations about 1200 patients are needed to detect a 24% reduction in primary outcome.

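### The stated 24% relative reduction is wrong: the plan's own risks (24% against 17.4%) give 27.5%, and 1222 patients have only about 69% power for a true 24% reduction

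*Protocol article*

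**What the plan says.** The section on sample size considerations builds the effect size from subgroups of the imaging arm.

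- Control group: "the 5-year-risk in the control group is assumed 24" per cent.
- Prevalence of the subgroups in the imaging arm: "estimated to be 8% for B; 70% for D and 22% for C".
- Untreated 5-year risk: for group B it "is 66% for those with stenosis of the left main coronary artery"; for the others, "32.8% for those with cardiac ischemia during the stress test (group C) and 16.4% for those without cardiac ischemia (group D").
- Assumed treatment effect: "70% reduction in 5-year event rate using reperfusion therapy (PCI/CABG) for group B", a 40% reduction for group C, and none for group D, which is not treated.

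From these inputs the section derives a risk of 17.4% in the intervention group, "reflecting an estimated relative reduction in cardiovascular morbidity and mortality of 24" per cent. The next paragraph gives 1222 randomized patients for 80% power at a two-sided alpha of 0.05.

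The design paragraph of the abstract carries the same effect size: "Based on sample size calculations about 1200 patients are needed to detect a 24% reduction in primary outcome".

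**The concern.** A fall from 24% to 17.4% is not a 24% relative reduction. The number given as the effect is the same as the control risk, so it may be a slip in copying, but the document does not show how it arose.

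The wrong percentage stands directly beside the power claim. The article names 24% and then says how many patients achieve that goal with 80% power. A reader will conclude that a true 24% reduction would be missed one time in five. If the trial is in fact sized for a larger effect, that chance is higher, and a null result would be read as stronger evidence against a 24% benefit than it is. The trial also plans three-monthly sequential analyses that may stop when no difference can be expected any more. Such a design rests on a stated reference effect, and the article does not say which value was used for it.

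**Working it through.** **Step 1. Rebuild the two risks from the subgroup inputs** (all from the section on sample size considerations).

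| Group | Share | Untreated risk | Contribution, untreated | Factor after treatment | Contribution, treated |
|---|---|---|---|---|---|
| B | 0.08 | 66% | 5.28% | 0.3 | 1.58% |
| C | 0.22 | 32.8% | 7.22% | 0.6 | 4.33% |
| D | 0.70 | 16.4% | 11.48% | 1 | 11.48% |
| Sum | 1.00 | | **23.98%** | | **17.39%** |

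Both sums agree with the stated 24% and 17.4%, so the two risks are sound.

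**Step 2. Relative reduction.**

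- Stated risks: (24 − 17.4)/24 = 6.6/24 = 27.5%.
- Unrounded sums: 1 − 17.39/23.98 = 27.5%. Rounding does not explain the gap.

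**Step 3. Which effect do 1222 patients fit?** The inputs are a two-sided alpha of 0.05, 80% power and 1:1 allocation (section on randomization), with a comparison of two proportions, because the statistical analysis section names a chi-square test of absolute risks. With p̄ the mean of the two risks and d their difference, the number per arm is

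n = [1.960·√(2p̄(1−p̄)) + 0.842·√(p₁(1−p₁) + p₂(1−p₂))]² / d²

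The unpooled version uses the second variance in both terms. The continuity-corrected version multiplies n by ¼[1 + √(1 + 4/(n·d))]². Totals are twice n, rounded up per arm.

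| Contrast | Relative reduction | Unpooled | Pooled | Continuity-corrected |
|---|---|---|---|---|
| 24% vs 17.4% | 27.5% | 1176 | 1182 | 1242 |
| 24% vs 18.24% (= 24% × 0.76) | 24% | 1570 | 1576 | 1644 |

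The planned 1222 lies inside the range of the first row and is 1.6% below its continuity-corrected value. It is about 350 to 420 patients short of the second row.

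**Step 4. Power with 611 per arm.** Power = Φ[(d − 1.960·√(2p̄(1−p̄)/611)) / √((p₁(1−p₁) + p₂(1−p₂))/611)]. The continuity correction subtracts a further 1/611 from d.

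- 24% vs 17.4%: (0.066 − 1.960 × 0.02318)/0.02310 = 0.890, so power is 81.3% (79.4% corrected).
- 24% vs 18.24%: (0.0576 − 1.960 × 0.02335)/0.02329 = 0.508, so power is 69.4% (66.9% corrected). A log-rank calculation with Schoenfeld's formula at the implied hazard ratio of 0.734 gives 70.1%.

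**Step 5. Other readings of the 24%.**

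- Keeping both 17.4% and a 24% reduction requires a control risk of 17.4/0.76 = 22.9%. This contradicts the stated 24% and gives about 67% power.
- Reading 24% as a hazard ratio of 0.76 gives about 60% power.
- It cannot be an absolute difference, which is 6.6 points, and the text calls it relative.
- A one-sided test at 0.05 of 24% against 18.24% needs 1240 patients, which is near 1222. But the sample size section states a two-sided alpha twice, and the statistical analysis section says that all tests are two-sided.

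**The case against.** The strongest reply is that nothing in the design depends on the wrong number. The two risks, alpha, power and sample size agree with one another. Against its own assumptions the trial is not underpowered, and the smallest effect detectable with 80% power at 1222 is about 27%. The full section prints both risks, so a careful reader can recover the true contrast. The 69% applies only to an effect that the subgroup model does not produce. The planned hazard ratio with its 95% confidence interval will show which effects are excluded, whatever the planning label says. Nothing shows that 24% was used as the reference effect of the sequential design.

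Most of this is right as far as it goes. The sample size suits the 24% against 17.4% scenario, and the 69% is conditional. It is also true that no variant returns 1222 exactly, and that the run of the sample size software is not shown. But none of this makes the statement correct. The misstated figure is the effect to which the power claim is attached, and it is the only effect size in the abstract, where the two risks are not given and it cannot be checked. That the reference effect of the sequential design is unstated is a reason to confirm it.

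**Conclusion.** The concern holds. By the article's own risks the planned relative reduction is 27.5%, not 24%, and the wrong value appears both in the sample size section and in the abstract. As written, the article claims 80% power for an effect at which 1222 patients have about 69% (67% with continuity correction), so the type II error is about 31% and not 20%.

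The arithmetic of the 27.5% needs no assumption beyond the stated risks. The power figures assume a two-sided 0.05 comparison of two proportions with 611 patients per arm, complete 5-year follow-up and one fixed-sample analysis. The sequential looks are not modelled and no dropout allowance is included. The trial remains adequately sized for 24% against 17.4%. That the 24% is the control risk repeated is plausible but not shown.

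**What to change.** In the abstract (design paragraph) and in the sample size section, replace the 24% reduction by a 27.5% relative reduction, from 24% to 17.4%, an absolute difference of 6.6 percentage points. Add one sentence saying that 1222 patients give about 69% power for a 24% relative reduction in a fixed-sample calculation. Confirm which reference effect was entered in the sequential design, and state it.

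If the sponsor did intend to detect a 24% reduction, the risks and the sample size must be reworked instead: 80% power would then need about 1570 to 1644 patients before any adjustment for the sequential design.

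The first course is a wording correction in two places. It needs no new patients and makes the advertised detectable effect less favourable. With 228 patients enrolled when the article was written, either course was still open.

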### Randomization

Randomization will be performed per hospital to ensure an equal distribution of groups of patients within hospitals. Directly after the patient gives informed consent, he or she is randomized with the use of the randomization module at the GROUND website. Only the data management center is aware of block size. This way half of the patients will be randomized for the imaging-with-treatment algorithm (groups B, C and D, figure 1), the other half of the patients (group A) undergoes only CT calcium scoring and enters follow-up. Patients randomized for the treatment groups (groups B, C and D, figure 1) will be scheduled for MDCT angiography. If a stenosis of the left main coronary artery (LM) (or equivalent) of more than 50% is observed on the CTA of a patient in the imaging-with-treatment group, he/she will be referred to a cardiologist for further diagnosis and treatment (group B, figure 1). A stenosis in the proximal left anterior descending coronary artery (LAD) in combination with a stenosis in the proximal circumflex coronary artery (LCX) is considered equivalent to a LM stenosis. All other patients in this group will undergo DSMR testing (groups C and D). Patients with a DSMR positive for ischemia are referred to a cardiologist for further diagnosis and treatment (group C). Further diagnostics and treatment will be left up to the cardiologist.

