### End points and follow-up

All patients will be asked to fill out a short follow up form every half year for a total period of five years. The occurrences of events are recorded. The quality of life assessment is based on the SF36 questionnaire and repeated after 12, 30, 48, and 60 months. This questionnaire has been validated in the Dutch population [40]. Endpoints of the GROUND study are in concordance with the SMART [41] study endpoints.

The term 'end points' is used to describe death, cardiovascular complications, and interventions. Apart from death the occurrence of an endpoint does not imply that the follow-up will be ended. Endpoints in the GROUND study are summarized as MACE: Major Adverse Clinical Events. Primary outcome is a composite endpoint comprising fatal and non-fatal myocardial infarction and stroke, and vascular death (death due to vascular disease). Secondary end points are: fatal and non-fatal myocardial infarction; fatal and non-fatal stroke; vascular interventions; amputation; aortic rupture; end stage renal failure extra cranial hemorrhage; complications of CABG or PCI and all cause mortality.

Reported endpoints are classified by the Endpoint Committee, which is unaware of the randomization allocation. Clinical information (letters of discharge) is obtained from the treating specialist or general practitioner. All reported endpoints enter an endpoint verification procedure. Copies of discharge records are sent to the members of the Endpoint Committee. The members of the Endpoint Committee do not share the information between each other, but classify the events independently. Only if discharge records are inconclusive further medical information is obtained (results from laboratory findings, copy of the ECG, copies of imaging reports). The classifications are compared. If two members do not agree the endpoint will be discussed with the blinded research physicians of the GROUND study group. They will decide or consult an extra physician, whose judgment is regarded as final.

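### The 1222 patients are a fixed-sample size, so under the double triangular test a cap at 1222 does not secure both 80% power and two-sided alpha 0.05

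*Protocol article*

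**What the plan says.** All of this is in the protocol article.

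- **Sample size considerations** gives the fixed calculation: "The total number of patients randomized to achieve this goal, with a two-sided alpha of 0.05 and 80% power will be 1222". The inputs are a control-arm 5-year risk of 24% and, for the other arm, "the 5-year risk of cardiovascular morbidity and mortality will be 17.4 % in the intervention group".
- The same paragraph states: "A study of this size has a statistical power of 80% at a two-sided alpha level of 0.05".
- It then introduces monitoring: "Sequential analyses are performed on survival outcome variables according to the double triangular test", carried out every three months in a different program from the one used for the sample size. The only reason given is a smaller number of patients on average. No maximum information or event number is stated, and nothing links the two calculations.
- **Statistical analysis** plans a chi-square comparison of absolute risks, with a Cox model in addition, judged two-sided at p < 0.05. It does not refer to the sequential design.
- **Randomization** gives 1:1 allocation ("This way half of the patients will be randomized for the imaging-with-treatment algorithm"), and **End points and follow-up** gives five years of follow-up per patient.

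**The concern.** A double triangular test gains a smaller expected sample size by accepting a larger maximum. If the number recruited is fixed by a single-look formula, the data can run out before the boundaries meet. A trial that ends in that gap needs a decision rule. If it counts as inconclusive, power falls below the stated figure. If it is tested as though there had been no earlier looks, the type I error rises above the stated figure. The article gives power and alpha as a pair for a study of this size, so the question is whether both hold under the monitoring it names.

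**Working it through.** **Inputs.** Risks of 24% and 17.4%, two-sided alpha 0.05, power 80%, 1222 patients (Sample size considerations); 1:1 allocation; 5 years of follow-up; looks every three months. Assumed, because the article does not say: the sequential design uses the same alpha, power and reference effect, and there are 20 to 40 looks (five years alone is 20; accrual time is not stated).

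**1. Reproduce 1222.** With p̄ = 0.207 and difference 0.066:

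n per arm = [1.96·√(2·0.207·0.793) + 0.8416·√(0.24·0.76 + 0.174·0.826)]² / 0.066² = 590.4, or 1181 in total.

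With continuity correction it is 620.3 per arm, or 1241 in total. The stated 1222 lies between the two. A single-look chi-square test with 611 per arm has 81.3% power. So 1222 is a fixed-sample figure.

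**2. Information on the survival scale.**
- Hazard ratio = ln(0.826)/ln(0.76) = 0.697, so θ = 0.3616.
- Fixed-sample information V = (1.96 + 0.8416)²/0.3616² = 60.0, which is 4 × 60 = 240 events.
- 1222 patients give 611 × (0.24 + 0.174) = 253 events, V = 63.

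**3. Maximum information of the double triangular test.** Use one-sided alpha 0.025 on each side and rescale the reference effect to 80% power: θ′ = 0.3616 × 2 × 1.96/(1.96 + 0.8416) = 0.506.
- Continuous monitoring: a = (2/θ′)·ln 20 = 11.84, c = θ′/4 = 0.1265, V at closure = a/c = 93.6. The ratio is 93.6/60.0 = 1.56, about 374 events.
- N discrete looks: V = [√(4·0.583²/N + 8·ln 20) − 2·0.583/√N]²/θ′². For N = 20 this is 4.642²/0.506² = 84.2, a ratio of 1.40. For N = 30 the ratio is 1.43, and for N = 40 it is 1.45. That is about 336 to 348 events (1.40 × 240 and 1.45 × 240).

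So 253 events are about 73 to 75% of the discrete-look maximum (253/348 and 253/336).

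**4. Simulation.** The score statistic has drift θ and variance V. Stop for a difference when |Z| ≥ a + cV − 0.583√ΔV. Stop for no difference when |Z| ≤ −a + 3cV + 0.583√ΔV.

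Run to completion, the test has 80.7% power at alpha 0.05 and uses on average 0.69 to 0.70 of the fixed information (about 166 to 168 events). The design itself therefore works as intended.

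Cut off at 1222 patients, under the planned effect, about 74% cross for benefit, about 16% stop for no difference and 9 to 10% are undecided (three-monthly looks, accrual over 3, 4 or 6 years). If 1222 gave only the fixed-sample V = 60, about 12 to 13% would be undecided.

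| Handling of an undecided trial | Power | Overall two-sided alpha |
|---|---|---|
| Only boundary crossings count | about 74% (range 72 to 75%) | below 0.05 |
| Critical value raised (about 2.11 to 2.16) to hold alpha | 76.5 to 78% | 0.05 |
| Unadjusted p < 0.05 | about 80% (79.5 to 81%) | about 0.054 to 0.06 |

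The lower power figures take V = 60 at the cut-off, the upper ones V = 63. The lower alpha lets events under the null rise to 611 × 0.48 = 293; the higher one holds information at the planned-effect level.

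**The case against.** The strongest reply is that the Statistical analysis section already supplies a final test. About two thirds of the undecided trials have z above 1.96 at the end, and counting them brings power back to about 80%. This stands, and it means that about 74% is not the power of the plan as written. But that test takes no account of the interim looks, and the price is an overall alpha above 0.05. The reply rescues one half of the stated pair at the expense of the other.

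A second reply is that the sequential settings, the maximum information and the rule for an undecided trial usually sit in fuller documents, and that 1222 is not called a hard cap. That is fair, and their absence alone would be no finding. What remains is a positive statement: 80% power at alpha 0.05 for a study of this size, followed at once by a monitoring rule under which that pair does not hold at that size.

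Three stronger readings are tempting and not supported:
- **That the maximum is 56% larger.** This is the continuous-monitoring limit; the article fixes three-monthly looks, which give about 40 to 45%.
- **That an excess of that order means a large loss of power.** It does not, because most trials stop well before the maximum.
- **That power is only about 61%, the crossing probability for a true 24% reduction.** That figure borrows a separate discrepancy: 24% against 17.4% is a relative reduction of 1 − 17.4/24 = 27.5%, not the stated 24%. Even a fixed design of 1222 has only about 69% power for a true 24% reduction. That matter should be raised on its own.

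**Conclusion.** The point holds at moderate weight. The figure of 1222 is a fixed-sample size, and the trial is monitored by a test whose maximum information is about 1.40 to 1.45 times larger. If 1222 is a cap, 80% power and two-sided alpha 0.05 do not both hold: the cost is about 2 to 3.5 power points below the stated 80% at preserved alpha, or an alpha excess of about 0.005 to 0.01. A reader might infer that the trial is badly underpowered or must recruit several hundred more patients; these figures do not support that. The article's claim that the sequential design needs fewer patients on average is correct.

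The conclusion rests on two assumptions: that the sequential design uses the one set of alpha, power and effect the article states, and that recruitment ends at 1222 with five years of follow-up. If other settings were used, the sizes above change, and the 80% statement would not describe the monitored design.

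**What to change.** 1. State that 1222 is the fixed-sample size, and say whether it is a cap on recruitment.
2. Give the parameters of the double triangular test (alpha, power, reference effect), with its maximum and expected numbers of events. Under the assumptions above these are about 336 to 348 and 166 to 168.
3. In Statistical analysis, replace the unadjusted p < 0.05 test of the primary outcome with an analysis that accounts for the sequential design, and fix in advance how it is done when the data end with no boundary reached.
4. Restate the power at alpha 0.05 for that analysis. With a cap at 1222 it is about 76.5 to 78%.

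This keeps the double triangular test, and with it the stated aim of stopping when no difference can be expected. Alpha spending without a futility rule would give up that aim. The cost is a recalculation in software already in use and a few sentences of text, with no extra patients. The Conclusion section reports 228 patients included, so the change can still be made early in recruitment; it should be made without reference to unblinded interim results.
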